#### Statistical analysis

IBM SPSS 26 data software manager will be used to perform quantitative data analysis. The analysis for the pre-post evaluation study will focus on two outcome variables: (a) changes in hospital self-harm repetition rates, overall and in the two subgroup of high-risk patients, and (b) changes in rates of mental health assessments being conducted with self-harm patients. To analyse changes in the overall hospital self-harm repetition rates, Poisson regression will be used to compare the mean proportions of self-harm repetition rates at baseline, 6 and 12 months follow-up, using a moving window. This analysis will also address differences between the subgroups of major self-harm repeaters and high-risk patients. Hospital self-harm assessment attendance rates at baseline, 6 and 12 months follow-up will also be analysed using Poisson regression. Adjustment of relevant variables, such as services availability, type of hospital, staff trained, etc., will be made during the analysis.

Thematic analysis will be used in order to analyse qualitative data from the focus groups [28]. Data analysis software manager QSR NVivo 12 will be used to assist in the analysis of the dataset, which consists on transcripts from the focus groups.

#### Sample size and power calculation

Using 2017 as an example, there were 11,600 hospital-based self-harm presentations, involving 9103 individuals, across the 27 hospitals in Ireland [2]. The proportion of acts accounted for by repetition in 2017 was 21.5%. Of the 9103 self-harm patients treated in 2017, 1322 (14.5%) made at least one repeat presentation to hospital during the calendar year [2]. It is expected that similar numbers will arise from the 3-year average rates from 2016, 2017, and 2018. In order to achieve the anticipated reduction from 12 to 8% reduced self-harm repetition rate, which will be detected by achieving 90% power at 0.05 significance level, it is expected that enough cases will be identified throughout the 27 hospitals collected at baseline and at 6 and 12 months follow-up, following patterns of data from 2017.

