## Background

Self-harm and suicide are major public health concerns. Worldwide over 800,000 people die due to suicide every year and is the second leading cause of death among young people [1]. For each suicide, there are more than 20 suicide attempts [1]. In 2018, the National Self-Harm Registry of Ireland (NSHRI) recorded 12,588 hospital presentations due to self-harm nationally, involving 9785 individuals [2]. Compared to 2017, self-harm hospital presentations in Ireland have increased by 7%. Furthermore, over 22% of patients repeated self-harm. Similar increasing trends have followed worldwide [3], although certain decreasing rates have been reported [4]. Furthermore, there was a significant increase in certain highly lethal self-harm methods used, such as attempted hanging, which increased by 24% from 2017 [2]. Self-harm is one of the strongest risk factors for both non-fatal self-harm repetition and suicide, with evidence indicating certain groups being more prone to repeat self-harm and/or die by suicide (e.g. men, young people, older age groups, people engaging in more lethal self-harm methods and those with a history of 4 or more previous presentations) [5, 6].

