### Phase 2: implementation of the SAMAGH training Programme

An invitation to participate in SAMAGH will be sent to a representative group of 40 to 50 health professionals (Clinical Nurse Specialists, Non-Consultant Hospital Doctors, Psychiatry Registrars, Clinical Psychologists, Psychiatrists, among others) working across the 27 public hospitals in Ireland. Given that the SAMAGH Training Programme does not have a special focus on children, children’s hospitals will not be included in the recruitment of health professionals. Each group of health professionals will have representatives from a range of different hospitals across Ireland. Attending the SAMAGH training is not compulsory for health staff. SAMAGH will be delivered to groups of 8–10 participants, and there will be approximately five groups in total. It is expected that health professionals who complete the training will incorporate the learned skills and knowledge in their daily practice with self-harm patients.

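### The power statement starts from a 12% repetition rate that matches neither 2017 rate in the same paragraph, and its 90% does not describe what the study can detect

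*Protocol article*

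**What the plan says.** The section on sample size and power calculation in the protocol article gives two repetition rates for 2017. One counts persons: "Of the 9103 self-harm patients treated in 2017, 1322 (14.5%) made at least one repeat presentation to hospital during the calendar year". The other counts acts: "The proportion of acts accounted for by repetition in 2017 was 21.5"%. It expects the 2016 to 2018 average to be similar. It then plans on an "anticipated reduction from 12 to 8% reduced self-harm repetition rate, which will be detected by achieving 90% power at 0.05 significance level", and concludes that "it is expected that enough cases will be identified throughout the 27 hospitals collected at baseline and at 6 and 12 months follow-up".

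The outcome is a national aggregate over 27 hospitals (Outcome evaluation). Training is voluntary and goes to "a representative group of 40 to 50 health professionals" (Phase 2). The Background gives a further figure for 2018: "over 22% of patients repeated self-harm".

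**The concern.** A planning rate should be the expected baseline of the outcome to be analysed. Here 12% stands beside two observed rates, agrees with neither, and has no metric, window or source attached. The outcome and analysis sections refer only to repetition rates, so they do not settle which rate is meant.

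The effect is also a one-third fall in a national figure, although the intervention reaches patients only through a limited number of trained staff. This is the only planning figure in the article. A reader who takes it as a general 90% could treat a null national result as evidence that the training failed, when the true national change may have been well below the one the 90% refers to.

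**Working it through.** **Inputs from the article.** 2017: 11,600 presentations, 9,103 persons, 1,322 persons with a repeat. 2018: 12,588 presentations, 9,785 persons. Planned effect 12% to 8%, power 90%, significance level 0.05.

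**Assumptions.** Two-sided test (sidedness is not stated). Persons independent. Baseline 3 × 9,103 = 27,309, treating each year's patients as distinct. Six-month follow-up 9,103/2, about 4,550.

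**1. The rates.**
- Persons: 1,322/9,103 = 14.5%.
- Acts, 2017: (11,600 − 9,103)/11,600 = 21.5%.
- Acts, 2018: (12,588 − 9,785)/12,588 = 22.3%.

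Both 2017 figures reproduce, and neither is 12%. The Background's figure for patients is in fact the share of acts.

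**2. The stated power.** For two proportions with mean p̄, n per period = [1.96√(2p̄(1−p̄)) + 1.2816√(p₁(1−p₁) + p₂(1−p₂))]² / (p₁−p₂)².
- 12% v 8%: (1.96√0.18 + 1.2816√0.1792)² / 0.0016 = (0.8315 + 0.5425)² / 0.0016, about 1,180.
- Available: 9,103 a year, or 9,103/1,180 = 7.7 times the need.
- Power at 12% v 8% exceeds 99.9% for 27,309 v 9,103 and for 27,309 v 4,550.

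So 90% is not the power at the stated effect. It holds only as a lower bound.

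**3. Does correcting the baseline matter for power?**
- 14.5% to 9.67% (same one-third fall): about 954 per period.
- 14.5% to 10.5% (same 4 points): about 1,435 per period.

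Both are far below 9,103, so power is not reduced.

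**4. What could be detected.** Smallest change at 90% power ≈ 3.24 × √[p(1−p)(1/n_b + 1/n_f)], with p = 0.145.
- 12 months, 27,309 v 9,103: standard error 0.426 points, giving 1.38. Solving with the lower follow-up rate gives 1.36, so about 1.4 points.
- 6 months, 27,309 v 4,550: standard error 0.564 points, giving 1.83 (solved: 1.79), so about 1.8 points. This uses 14.5% for want of a six-month rate.

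**5. Illustration of year-to-year variation (SD assumed, not in the article).** Add SD² × (1 + 1/3) to the variance at 12 months.
- SD 0.5: 3.24 × √(0.182 + 0.333) = 2.3 points.
- SD 1.0: 3.24 × √(0.182 + 1.333) = 4.0 points.

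**6. Illustration of coverage (share assumed, not in the article).** If trained staff see a share s of patients and cut repetition in them by one third, with no spread to other staff, the national change is 14.5 × s/3 points.

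| s | National change (points) | Power, 27,309 v 9,103, independence |
|---|---|---|
| 10% | 0.48 | 20% |
| 20% | 0.97 | 63% |
| 30% | 1.45 | 93% |
| 50% | 2.42 | >99% |

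**The case against.** The strongest defence is that the sentence claims only enough cases for 90%, and that claim is met nearly eightfold before any allowance for clustering or overdispersion. This stands. A reader might infer that the wrong baseline leaves the study underpowered; step 3 shows that it does not.

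Nor is 12% proven false. The analysis section mentions a moving window, and another window could give another rate. The article does not say so, however, so the figure remains undefined and unreconciled with its neighbours. The absence of a stated sample size or formula is no fault in a condensed article.

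A reader might also infer that 40 to 50 staff cannot produce a one-third national fall, or that it is arithmetically impossible. The documents do not support this. They give no share of patients seen by trained staff. Seeing one third of presentations would take 11,600/3/50 = 77 to 11,600/3/40 = 97 per trained person per year, and the invited groups include clinical nurse specialists and psychiatrists. Spread to untrained colleagues is possible too. The plan also adjusts for staff trained and measures adherence at 12 months, which would help in reading a null result. What remains is that the national effect is assumed with no link to coverage.

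**Conclusion.** The point holds in limited form. The 12% contradicts the rates and the expectation stated in its own paragraph, with no metric or window to explain it. The 90% is true only as a floor for a 4-point fall, where power under independence is above 99.9%. It neither describes what the study can detect nor covers smaller national effects.

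Under independence the detectable change from 14.5% is about 1.4 points at 12 months and 1.8 at 6 months. These figures rest on 2017 volumes, distinct patients across years and no clustering by hospital, so they are optimistic. The 2.3 to 4.0 points and the power figures by coverage depend on assumed inputs and are illustrations only. The Background wording is a minor separate correction that does not feed the power statement.

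**What to change.** - Name one repetition metric and window, for example the person-based calendar-year rate (14.5% in 2017), and use the registry baseline for that definition.
- Replace the 12 to 8% statement with the smallest national change detectable at 90% power from that baseline: about 1.4 points at 12 months and 1.8 at 6 months under independence. Widen both using year-to-year and between-hospital variation estimated from the registry's 2016 to 2018 data.
- Express the assumed national effect as coverage share × effect in patients seen by trained staff, over a range labelled as assumption, and note possible spread to other staff. Do not call the study 90% powered for smaller effects.
- In the Background, state that over 22% of presentations, not patients, were repeat acts.

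The cost is rewording one paragraph and one Background sentence, plus a short calculation on registry data already planned for use. No extra data or patients are needed.

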### Data management and access

The protocol complies with the Irish Data Protection Act of 1988 and the Irish Data Protection Amendment Act of 2003 and General Data Protection Regulation (2018). Only anonymised data will be released in aggregate form in academic journal articles, conference papers, and reports.

The Pre Training questionnaire and the 12-month online questionnaire will be conducted using the E-learning Website and Survey Monkey, which can be completed without providing any contact or personal information.

Existing protocols will be followed to ensure maintaining patient confidentiality. No details that would allow identification of participants will remain anywhere but in the consent forms, which will be securely stored.

The hard data from focus groups will be assigned ID numbers and the code key of participants’ names will be kept in a separate locked cabinet. Electronic data will be password-protected and stored on an encrypted computer within offices to which only NSRF staff have swipe access. Participants will be permitted access to their personal data at any time and will be entitled to withdraw their data from the study up to the point of publication. Manual data and electronic data will be stored securely in locked cabinets and encrypted computers within the NSRF offices for 10 years after collection.

### Precautions

The researchers involved are experienced in the area of mental health research and have received specialised in-house training in relation to responding to distress and risk in the context of face-to-face contact. The researchers will receive weekly supervision from the Principal Investigator (PI), [name].

Participants will be fully informed of the aims and procedure of the research and researchers will be mindful of potential risk. Specific arrangement for participants will be made if required. Participants can consult with the PI, [name]. Interviewer safety will be taken into account at all times. Debriefing sessions will be held with the PI (a trained psychotherapist, [name]) and the involved researchers on a weekly basis or more regularly if required.

## Discussion

Interventions aimed at reducing hospital-based self-harm presentations and hospital support received are crucial for self-harm patients and society. Identifying and managing high-risk hospital self-harm presentations is key for prevention of repeated self-harm and suicide [1]. Repeated self-harm presentations remain an ongoing challenge in hospital settings, both in Ireland and globally [1–5]. A numerable amount of such hospitalisations could be prevented by improving care and support given to self-harm patients presenting to hospital. To our knowledge, this is the first study to address improving care and support given to the clinical subgroups of at risk self-harm patients: major self-harm repeaters and high-risk self-harm (HSRH) patients, as well as evaluate the training programme through a process and outcome evaluation. In addition to a direct contribution to health care at a national level, it is expected that this study will contribute to the development of suicide prevention and intervention programmes. This study is also expected to contribute to self-harm and suicide training capacity building activities, with the possibility of being translated to other settings.

## Data Availability

Not applicable.

## Abbreviations

HRB: Health Research Board
HSRH: High-risk self-harm
IMPRESS: Improving Prediction and Risk Assessment of Self-harm and Suicide
MRC: Medical Research Council
NSHRI: National Self-Harm Registry of Ireland
NSRF: National Suicide Research Foundation
SAMAGH: Self-harm Assessment and Management programme for General Hospitals
SSIS-ACE: Psychological, psychiatric and work related risk factors associated with suicide in Ireland
UCC: University College Cork
